### Biomarker outcomes

Transcriptomic and proteomic profiling on blood at convalescence (2 weeks and 26 weeks), compared with acute baselines, and on CSF at 2 weeks compared with acute baseline.Anti-NMDA receptor antibody testing at 26 weeks.

### Safety outcomes

Proportion of patients with detectable HSV in CSF by PCR at 2 weeks.

Health Status and Quality of Life (at 26 and 78 weeks):

Measured by the EuroQoL-5 Dimension-5 Level quality of life scale and 36 item Short-Form Survey self-completed questionnaires.

### Screening

The majority of potential patients are identified by the local research team through identifying patients with a relevant clinical presentation suspicious of HSV encephalitis and/or detection of HSV in a CSF sample. A screening log is completed for all potential patients. A strong link with the local laboratory is essential as a key factor in ensuring eligible patients are not missed by the investigative team. Investigators for the local research team include neurologists, infectious disease clinicians, acute medics, microbiologist and virologists.

Because this is a rare disease, most centres will only see 1-2 potential patients a year. Extra measures have therefore been taken to try and maximise recruitment. On identifying a suitable patient, sites are able to contact the trial management team for intensive support via a dedicated telephone hotline, email, or an app. Short videos which explain the trial to patients, families and to healthcare workers also support recruitment. Every month, the trial management group monitor the screening reports of each site for the previous 3 months, to ensure they are actively looking for patients. Lower than expected screening is followed up by the central study team making contact with the study site to review their screening methodology and offer support.

### Randomisation

Participants are randomised using a 24-hour secure web-based programme, which is centrally controlled by the clinical trials research centre. Designated members of the trial team at the site (detailed on the delegation of responsibilities log) are provided with a unique username and password which is required to access the web-based randomisation system. In the event of system failure, the patient can be randomised centrally electronically or through secure envelopes. Each participant is allocated a unique study number (randomisation number), the primary identifier for all the participants in this study.

The neuropsychologist collecting the primary outcome and other outcome assessors such as radiologists and the lead investigators are blinded to randomisation during the trial. Trial participants and local site study teams, as well as the trial manager and trial data manager at the clinical trials unit are aware of what treatments have been allocated. The independent data safety and monitoring committee (IDSMC) and statisticians have access to unblinded data grouped by intervention throughout the trial and make recommendations to the trial’s steering committee who would only become unblinded in the event of a serious event.

### Participant timeline

The time schedule for enrolment, interventions and assessments is given in table 1.

**Table 1 T1:** Time scale for patients randomised in the DexEnceph study

Procedures	Inntervention and follow-up schedule						
	Screening	Baseline	2 weeks	Discharge or day 30 of admission (whichever is sooner)	26 weeks	78 weeks	Premature discontinuation
Signed consent form	X*	X†					
Assessment of eligibility criteria	X	X†					
Review of medical history		X†					
Review of concomitant medications		X†	X	X	X	X	X
Physical exam		X		X			
Study intervention		X					
Clinical data collection		X		X	X	X	
MRI scan		X‡	X		X	X	
Research blood testing		X	X		X		
Lumbar puncture		X§	X				
Disability and functional outcomes				X	X	X	
Glasgow Coma Scale		X¶†	X¶	X¶	X	X	
Addenbrooke’s cognitive examination				X	X	X	
Neuropsychology assessment, including verbal memory score					X	X	
Health status and quality of life questionnaires					X	X	
Clinical laboratory: haematology, biochemistry		X**					
Assessment of adverse events			(X)	(X)	(X)	(X)	(X)

(X)—As indicated/appropriate.

*Only applicable when patients are prospectively consented for the randomised controlled trial.

†Procedures required before randomisation.

‡Baseline MRI done for clinical purposes can be done from hospital admission up to 7 days after randomisation.

§Diagnostic lumbar puncture for clinical purposes done prior to randomisation.

¶Recorded prior to randomisation, daily for the first 14 days and then weekly until discharge/30 days (whichever sooner).

**Recording of clinic al laboratory tests done for clinical purposes, not as part of trial.

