The pathogenic mechanisms in HSV encephalitis are not fully understood. The evidence suggests that in addition to direct viral pathogenesis, inflammation of the brain in response to the virus is a key component of the disease process.^18–21^ This is supported by the observation that in the cerebrospinal fluid (CSF), higher levels of proinflammatory chemokines, especially monocyte chemotactic protein-1, interferon γ and interleukin 6 (IL-6) are associated with a worse prognosis.^22 23^ Poor prognosis is also associated with the extent of inflammation seen on neuroimaging,^24^ and the degree of temporal lobe swelling is correlated with the severity of verbal memory impairment.^25^ Relapse occurs in about approximately 10% of HSV encephalitis patients, and is sometimes associated with the development of anti-N-Methyl-D Aspartic acid (NMDA) antibodies.^26^

Control of the inflammation in HSV encephalitis may improve outcome, as shown in mouse models of the disease.^27–29^ Before the availability of aciclovir, corticosteroids were sometimes used as a treatment in humans with HSV encephalitis,^30 31^ and more recently both cerebral oedema on imaging and CSF IL-6 levels were shown to be reduced in patients given corticosteroids.^23^ However, because corticosteroids cause immunosuppression, which in theory facilitates increased viral replication, their role is uncertain.^32^

In other brain infections, including bacterial meningitis and tuberculous meningitis the benefit of corticosteroids has been demonstrated in large clinical trials.^33^ For HSV encephalitis the potential benefit of using corticosteroid as an adjunct to aciclovir therapy has been suggested from small case series and retrospective comparisons, but there has been no prospective randomised study reported.^34–39^ One study, the German trial of Aciclovir and Corticosteroids in Herpes simplex virus Encephalitis (the GACHE trial) was stopped early because of poor recruitment rates.^40^ However, there is clearly a need for a study to answer this question. The DexEnceph Study, a randomised controlled trial of dexamethasone in HSV encephalitis, aims to achieve this.

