### Secondary objectives

Secondary objectives include the following:

To determine whether dexamethasone therapy has an effect on other neuropsychological, cognitive, clinical, disability and functional outcomes in HSV encephalitis.

To assess the effect of dexamethasone therapy on brain swelling examined by neuroimaging.

To determine whether dexamethasone therapy affects clearance of HSV from the CSF, the emergence of NMDA receptor antibody or causes any changes in transcriptomic and proteomic profiling in the CSF and blood.

A more comprehensive list of measures is detailed in the outcomes section.

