**Figure 1 F1:**
[figure not shown]
Schematic design of DexEnceph randomised controlled trial.

Participants assigned dexamethasone receive 10 mg equivalent of ordinary ward stock, prescribed by an authorised member of the local study team, given intravenously four times daily for 4 days (16 doses in total) starting within 24 hours of randomisation.

The University of Liverpool employs a clinical trials unit to be responsible for screening, and monitoring data collection, quality and completeness. As there is a low number of participants to be recruited, the trials unit are able to liaise regularly with each site following randomisation to ensure all follow-up data are collected. Primary outcome is recorded by a centrally employed roving neuropsychologist, who collects the neuropsychological outcomes at 26 and 72 weeks.

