### Clinical Outcomes

Incidence of epilepsy.Time to hospital discharge.Requirement of high-dependency unit or intensive care unit admission up to 30 days after randomisation.Time taken to be free of ventilatory support for 14 days (if any).Time to reach maximum recorded Glasgow Coma Scale score.Survival.

Disability and functional outcomes (at discharge or 30 days if still in hospital, 26 weeks and 78 weeks):

Modified Rankin Score, Barthel Index, Liverpool Outcome Score and Glasgow Outcome Scale Extended.

Imaging Outcomes: Change from Baseline at 2 weeks, 26 weeks and 78 weeks

Temporal lobe volume (as percentage of intracranial volume).Whole brain volume (as percentage of intracranial volume).Volume of affected region as seen on fluid-attenuated inversion recovery image (as percentage of intracranial volume).Volume of affected region as seen on diffusion-weighted image (as percentage of intracranial volume).

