### Statistical analysis

For the primary outcome, participants are included in the analysis based on the intention-to-treat principle. Verbal memory score will be compared between groups using linear regression. The model will be adjusted for prespecified variables which are judged to be potentially related to the outcome, including age and admission Glasgow Coma Scale Score. No interim analysis is planned, but there is regular monitoring by the IDSMC.

As there may be some missing primary outcome data due to death, inability to complete the assessment, or loss to follow-up, a sensitivity analysis will be carried out. All randomised patients will be included in this analysis.

For continuous secondary outcome variables, comparisons between groups will be analysed as per the primary outcome. The results for residual viral presence in the CSF at 2 weeks will be reported with a 95% CI for the difference in proportions between groups. Time to event outcomes will be analysed using Kaplan-Meier curves, log rank tests and Cox proportional hazards models. Binary secondary outcomes will be analysed using logistic regression.

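### The baseline MRI may be taken up to 7 days after randomisation, when the dexamethasone course can already be over, so the change-from-baseline imaging outcomes can be biased by an unknown amount

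*Protocol article*

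**What the plan says.** All references are to the protocol article.

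- **Participant timeline, Table 1.** The footnote to the baseline MRI reads "Baseline MRI done for clinical purposes can be done from hospital admission up to 7 days after randomisation". Other baseline items carry a different mark, explained as "Procedures required before randomisation"; the MRI does not. The diagnostic lumbar puncture has its own footnote placing it before randomisation.
- **Intervention (text under Figure 1).** Dexamethasone is "given intravenously four times daily for 4 days (16 doses in total) starting within 24 hours of randomisation".
- **Clinical Outcomes.** The heading is "Imaging Outcomes: Change from Baseline at 2 weeks, 26 weeks and 78 weeks". Four measures follow, each as a percentage of intracranial volume: temporal lobe, whole brain, affected region on FLAIR, and affected region on DWI.
- **Secondary objectives.** One aim is "To assess the effect of dexamethasone therapy on brain swelling examined by neuroimaging".
- **Introduction.** On earlier evidence in patients: "both cerebral oedema on imaging and CSF IL-6 levels were shown to be reduced in patients given corticosteroids".
- **Statistical analysis.** "For continuous secondary outcome variables, comparisons between groups will be analysed as per the primary outcome". That means linear regression. The section does not distinguish baseline scans taken before dosing from those taken after.

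**The concern.** A baseline should be fixed before treatment can act on it. Here the schedule expressly lets it be measured after the first dose, and even after the last. The article itself cites reduced oedema on imaging with corticosteroids. If that holds, a scan taken during or after the course in a dexamethasone patient already contains part of the effect that the outcome is meant to measure. Subtracting it removes that part. Entering it as a covariate instead would adjust for a post-randomisation variable.

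The open-label design adds a second route. Local teams know the allocation, and these scans are done for clinical reasons, so whether and when a scan follows randomisation could differ between arms. Blinded reading of the images does not protect against that.

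At stake is the secondary objective on brain swelling, and the reading of the later brain volume results as evidence on tissue loss.

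**Working it through.** **1. The plan's own figure.** The imaging outcomes have no power statement. The only powered figure is for verbal memory: difference 15.5, SD 23.1, two-sided 0.05, 36 per group. The noncentral t distribution gives 80.2% power at 36 per group, and 36 / (1 − 0.20) = 45 per group, 90 in total. This reproduces the plan, and no baseline MRI enters it.

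**2. Timeline (days from randomisation).**

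- Start: day 0 to day 1. The 4-day course ends between 0 + 4 = day 4 and 1 + 4 = day 5.
- With doses spaced 6 hours apart (assumed), the 16th dose falls at 15 × 6 = 90 h to 24 + 90 = 114 h, that is day 3.75 to 4.75.
- The MRI window closes on day 7, so a permitted baseline can fall 7 − 5 = 2 to 7 − 4 = 3 days after the whole course.
- Such a scan is only about 14 − 7 = 7 days before the 2-week scan.

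**3. Reach.** 4 measures × 3 time points = 12 comparisons, all sharing the same baseline scan.

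**4. Size at 2 weeks.** Let D be the true between-arm difference at follow-up, f the share of dexamethasone-arm baselines taken post-dose, and s the average share of D already present at those scans. The expected difference in change is D − f·s·D = D(1 − f·s), so the proportional loss is f × s. The article gives neither input; the values below are assumptions chosen to show the range.

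| f | s = 25% | s = 50% | s = 100% |
|---|---|---|---|
| 0 | 0% | 0% | 0% |
| 10% | 2.5% | 5% | 10% |
| 25% | 6.25% | 12.5% | 25% |
| 50% | 12.5% | 25% | 50% |
| 100% | 25% | 50% | 100% |

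**5. Direction at 26 and 78 weeks.** If treatment has lowered a volume by e at the post-dose scan, the mean baseline in the dexamethasone arm falls by f·e, and the between-arm difference in change shifts upward by f·e.

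- *Temporal lobe and whole brain volume.* Later loss from a lowered start looks smaller, which can appear as less atrophy with dexamethasone.
- *FLAIR and DWI lesion volumes.* Later shrinkage from a lowered start looks smaller. If shrinkage is the favourable direction, this counts against dexamethasone.

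The same mechanism therefore favours dexamethasone on two measures and works against it on the other two.

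**The case against.** The strongest reply is that the footnote sets an outer limit and does not describe usual practice. The window opens at hospital admission. Randomisation follows a positive CSF PCR that may have been reported up to 7 days earlier, and the Discussion allows for PCR delay and transfer between hospitals. A clinical MRI can easily come before randomisation. This stands: f may be close to zero, and a reader who infers that every imaging outcome is contaminated goes further than the document allows. The same holds for any single figure for the loss, since f and s are both unknown.

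A second reply is that the choice of analysis baseline, and the handling of late scans, belong to a statistical analysis plan that is not shown. This stands in part. The absence of a handling rule is no fault of the article. The permissive window is different, because it is a stated rule that conflicts with the purpose of outcomes defined as change from baseline.

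A third reply concerns the biology. The Introduction supports reduced oedema on imaging, but says nothing about DWI lesion volume or how quickly an effect appears. This also stands, so the bias is conditional on an early drug effect on the measure concerned.

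A reader might extend the point to the baseline research blood, which Table 1 does not mark as required before randomisation. The support is weak: Biomarker outcomes describes the comparator as acute, and the consent section provides for early sampling under deferred consent.

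**Conclusion.** The concern holds in limited form. The schedule permits baseline scans during or after the dexamethasone course, and every imaging outcome at every time point is a change from that scan, so these outcomes can be biased. The 2-week loss is f × s, from 0 upward: 2.5–10% at f = 10% and 12.5–50% at f = 50%, with s between 25% and 100%. This assumes an early effect on the measure, and that patients scanned late respond like the others.

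Two stronger readings are not supported. A false late benefit across all imaging outcomes does not follow, because that direction fits only the two brain volume measures. Nor is the main result at risk: verbal memory at 26 weeks uses no baseline MRI, and the sample size rests on it alone. This is a should-fix for secondary outcomes.

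**What to change.** Define the imaging baseline for analysis as the last MRI before randomisation. Do not use a post-randomisation scan as baseline or as covariate; treat that patient's baseline as missing.

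Compare follow-up volumes at 2, 26 and 78 weeks by ANCOVA on the pre-randomisation volume, alongside the covariates already planned. Fill a missing baseline with the overall mean and add a missing indicator, so that all patients with a follow-up scan stay in. This is sound here because whether a pre-randomisation scan exists is settled before allocation and cannot depend on arm.

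Report the timing of the baseline scan relative to randomisation by arm, which shows directly how many scans fell after it.

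The cost is a change of wording in Table 1 and the imaging analysis, and some loss of precision where no pre-randomisation scan exists. That loss cannot be calculated from the article. With 82 of 90 patients recruited by June 2021, an analysis definition is the practical route and needs no new scans. It does need scan dates; the article does not say that they are recorded, though applying the 7-day window presupposes them.

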### Statistical considerations

#### Sample size

The primary outcome variable is verbal memory, assessed as part of WMS-IV. In one published series of adults who survived HSV encephalitis, 19 of 22 had memory impairment evident at follow-up, with verbal memory being most severely affected.^12^ In that study the mean (SD) verbal memory score was 88.9 (18.9) compared with the population mean (SD) of 100.^15^ This score can only be assessed in survivors, we estimate approximately 10% of patients in the trial will die before assessment of the primary outcome.^8 43 44^ In instances where the death is judged to be associated with encephalitis the verbal memory score is recorded as 40, (the lowest possible value which would be obtained even where a patient recorded no recall of any of the items administered in the memory subtests). Where the cause of death is thought to be independent of having encephalitis, those patients will be recorded as lost to follow-up. Similarly, for patients who are too unwell, due to encephalitis, to undergo the assessment, the score is recorded as 40. Decisions as to whether the reasons for death or non-completion of the measures were due to encephalitis will be made by an independent committee blinded to dexamethasone allocation. Adjusting the estimate of mean and SD from survivors, to include the 10% of patients that die having the lowest possible value of 40, gives a total population mean of 84.8, with a SD of 23.1. A final sample size of 36 participants per group allows us to detect a clinically meaningful difference of 15.5 on the verbal memory score with 80% power, at a two-sided significance level of 0.05. Allowing for up to 20% dropout gives an initial target sample size of 45 participants per group, for a total of 90.

### Statistical analysis

For the primary outcome, participants are included in the analysis based on the intention-to-treat principle. Verbal memory score will be compared between groups using linear regression. The model will be adjusted for prespecified variables which are judged to be potentially related to the outcome, including age and admission Glasgow Coma Scale Score. No interim analysis is planned, but there is regular monitoring by the IDSMC.

As there may be some missing primary outcome data due to death, inability to complete the assessment, or loss to follow-up, a sensitivity analysis will be carried out. All randomised patients will be included in this analysis.

For continuous secondary outcome variables, comparisons between groups will be analysed as per the primary outcome. The results for residual viral presence in the CSF at 2 weeks will be reported with a 95% CI for the difference in proportions between groups. Time to event outcomes will be analysed using Kaplan-Meier curves, log rank tests and Cox proportional hazards models. Binary secondary outcomes will be analysed using logistic regression.

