### Secondary outcomes

Other neuropsychological outcome measures (at 26 weeks and 78 weeks after randomisation):

Verbal memory score, determined by the WMS-IV, Auditory Memory Index, at 78 weeks after randomisation.Visual, Immediate and Delayed Memory by Indexes of the WMS-IV, processing speed and working memory subscales from the Wechsler Adult Intelligence Scale Fourth Edition.Higher executive function using the Trail Making Test.Anxiety and Depression symptom levels by the Beck Depression Inventory and Beck Anxiety Inventory.Subjective cognitive complaints using the Perceived Deficits Questionnaire.

Cognitive Outcome Measures (at discharge or 30 days if still in hospital, 26 weeks and 78 weeks).

Addenbrooke’s Cognitive Assessment III.

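### The stated 78-week comparison of neuropsychology scores names no use of the 26-week score of patients lost in between, so loss that differs by arm could bias it

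*Protocol article*

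**What the plan says.** The Statistical analysis section names the primary model, "Verbal memory score will be compared between groups using linear regression", and says that it is "adjusted for prespecified variables which are judged to be potentially related to the outcome, including age and admission Glasgow Coma Scale Score". It then extends this to later outcomes: "For continuous secondary outcome variables, comparisons between groups will be analysed as per the primary outcome".

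The first item under Secondary outcomes is "Verbal memory score, determined by the WMS-IV, Auditory Memory Index, at 78 weeks after randomisation". In Table 1 (Participant timeline) the row "Neuropsychology assessment, including verbal memory score" is marked at 26 and 78 weeks and not at baseline.

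Missing data are addressed in one place. The reason given is "As there may be some missing primary outcome data due to death, inability to complete the assessment, or loss to follow-up", and the response is that "a sensitivity analysis will be carried out. All randomised patients will be included in this analysis". This is written for the primary outcome, and its method is not given.

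Under Sample size, a verbal memory score of 40 is assigned to deaths attributed to encephalitis and to patients whom encephalitis leaves unfit for testing. The article does not say whether this holds at 78 weeks.

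**The concern.** A regression on 78-week scores alone uses only patients who have such a score. Someone tested at 26 weeks and lost afterwards contributes nothing, although the trial holds a measurement of the same scale for that person. With no baseline memory test, the 26-week score is the only earlier reading.

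Such a regression is sound if, given age and admission Glasgow Coma Scale score, being lost is unrelated to memory. That is a demanding assumption here, because poor memory can itself make follow-up harder. Participants and site teams also know the allocation (Randomisation section), so patterns of loss could differ between arms.

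At stake is the trial's evidence on whether any effect on verbal memory lasts. A lasting difference could be understated or overstated, and some precision given up, while data that would help are already collected.

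**Working it through.** **The plan's own figure.** SD 23.1, difference 15.5, 80% power, two-sided 0.05 (Sample size):

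- Normal approximation: n = 2 × (1.960 + 0.842)² × (23.1/15.5)² = 34.9, so 35 per group.
- The t-test gives 35.85, so 36 per group with 80.2% power. Then 36/0.80 = 45 per group.

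The stated size reproduces. The 20% drop-out allowance belongs to the 26-week outcome. The article gives no loss rate between 26 and 78 weeks.

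**Inputs for the 78-week check.** From the document: SD 23.1 and 45 per arm. Assumed, because the document does not give them:

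- correlation ρ between visits of 0.7 to 0.8;
- loss after 26 weeks of 10% to 19%;
- true difference of 8 points at both visits;
- where loss depends on memory, log-odds of loss rising by 1.2 per SD fall in the 26-week score.

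Covariates are left out. To the extent that age and admission Glasgow Coma Scale score explain memory, the bias would be smaller.

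**Formula.** Take normal scores with equal SD at both visits, and loss that depends only on the 26-week score. Let S be the 26-week mean of those still seen at 78 weeks minus the 26-week mean of everyone in that arm. Then

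expected single-visit difference = true difference + ρ × (S in dexamethasone arm − S in control arm).

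**Low scorers leave one arm only; loss in the other arm is random (S = 0).** Numerical integration gives S = 2.41 points at 10% loss and 4.35 points at 19%.

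| Loss | ρ | ρ × S | Control arm only: 8 − ρS | Dexamethasone arm only: 8 + ρS |
|---|---|---|---|---|
| 10% | 0.7 | 1.69 | 6.3 | 9.7 |
| 10% | 0.8 | 1.93 | 6.1 | 9.9 |
| 19% | 0.7 | 3.04 | 5.0 | 11.0 |
| 19% | 0.8 | 3.48 | 4.5 | 11.5 |

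**Same pattern in both arms.**

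- At 10% average loss, S is 2.05 (dexamethasone) and 2.77 (control). The bias is 0.7 or 0.8 × (−0.72), that is −0.5 to −0.6.
- At 19%, S is 3.79 and 4.89. The bias is 0.7 or 0.8 × (−1.10), that is −0.8 to −0.9.
- With no treatment effect, S is equal in the two arms and the bias is 0.
- For a true difference of 15.5, with a slope of 1 per SD, ρ of 0.5 to 0.85 and 10-20% loss, simulation gave about −0.6 to −1.4.

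**Random loss.** S = 0 in both arms, so there is no bias. With k = 45 × (1 − loss) seen per arm:

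- SE, single visit = 23.1 × √(2/k)
- SE, both visits = 23.1 × √(2 × [(1 − ρ²)/k + ρ²/45])

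At 10% loss (k = 40.5) this is 5.13 against 5.01 (ρ 0.7) or 4.97 (ρ 0.8). At 19% (k = 36.45) it is 5.41 against 5.15 or 5.07. The reduction is about 2 to 6%.

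**Using the 26-week score.** A joint model of both visits removes the ρ × S term and returns 8.0 in every case above. That follows from the set-up, since loss was made to depend only on the 26-week score. When 10% of patients were given 40 as encephalitis deaths, the joint estimate was off by up to about 0.5 points and still far closer to the truth than the single-visit estimate.

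**The case against.** A reader might infer that the plan throws away the 26-week scores of later drop-outs. The document does not say so. It names a comparison model and is silent on missing 78-week scores. Imputing from the 26-week score and then fitting the same regression would fit the text, the covariate list is open, and such detail is commonly left to an analysis plan, which is not shown here. The reference back to the primary outcome may also be meant to bring the all-randomised sensitivity analysis with it. This stands against any claim that data are discarded. It does not remove the point that the one method named makes no use of the 26-week score.

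A reader might also infer that memory-related drop-out by itself biases the 78-week result. It does not: the loss pattern must differ by arm, or there must be a treatment effect, and in the second case the bias is small against a standard error near 5. No part of the document shows arm-dependent loss. A blinded central neuropsychologist at both visits and close contact with sites work against loss.

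Two further points stand. If the score of 40 for patients whom encephalitis leaves unfit for testing applies at 78 weeks, the worst cases stay in the analysis and the biases above are too large. And the joint model's advantage is partly built into the calculation: it does not correct loss driven by decline after 26 weeks, nor help with patients lost before then.

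**Conclusion.** The point holds in a limited form. The method named for 78-week scores is a single-visit regression with no stated use of the 26-week score.

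Under the assumed 10-19% loss, correlation 0.7-0.8 and true difference of 8 points, memory-related loss confined to one arm moves the 78-week difference by about 1.7 to 3.5 points, towards or away from no effect according to the arm. With the same pattern in both arms the shift is under about 1 point. With random loss there is none, and the cost is a few per cent in standard error. All inputs except the SD and the group size are assumptions, and the direction of any bias cannot be predicted from the document.

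This is a cheap improvement to a secondary outcome. It is not an error in the primary result, and the documents do not support saying that the 78-week result will be biased.

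**What to change.** In the Statistical analysis section:

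1. State that neuropsychology scores measured at both 26 and 78 weeks are analysed in one repeated-measures model, with arm, visit, arm-by-visit, age and admission Glasgow Coma Scale score each by visit, and unstructured covariance. Read the 78-week difference from it. Alternatively, state multiple imputation using the 26-week score, followed by the regression already planned.
2. State that the score of 40, both for encephalitis deaths and for patients whom encephalitis leaves unfit for testing, applies to verbal memory at 78 weeks.
3. State that the all-randomised sensitivity analysis also covers 78 weeks.

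The 26-week primary analysis stays as it is. The cost is a few sentences and standard software, with no new data or patients. The remaining weakness is the assumption that loss depends on observed scores. It is weaker than the one the single-visit regression needs, but it leaves later unobserved decline uncorrected.
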